# **Key Outcomes of Interest**

This study will measure VEA program impact on a set of primary outcomes outlined in the stated goals of the VEA program based on the midline data, including: (i) access to higher quality water; (ii) use of improved sanitation; and (iii) reduced burden of carrying water (in time spent carrying water). In addition, it will investigate a set of secondary outcomes including willingness to pay for water, improved health behaviors, child illness, hygiene practices, and school attendance, and local water and sanitation governance, among others.

In the midline survey, several outcomes will be measured indirectly. For example, one primary outcome is water quality, which will be measured indirectly, by capturing whether the water source is considered “improved” or not (i.e. boreholes are considered improved while unprotected springs or surface water sources are not). However, in the endline round of data collection we plan to measure water quality directly with microbiological testing. These direct measures are still being developed and field-tested and will be submitted through an addendum to the pre-analysis plan before the endline data collection.

Similarly, capturing biomarkers (e.g. anthropometrics, stool samples, anemia blood tests) is the most objective and accurate way to measure health impacts, particularly in settings like WASH interventions where the treatment group cannot be blinded to the intervention and often suffers from social desirability bias where respondents receiving the intervention over-report positive health impacts. However, biomarkers are costly and logistically challenging to implement. Since a number of recent studies have found limited impacts in biomarker measures because of small changes in intermediate outcomes, we propose a phased approach.

Some intermediate, self-reported outcomes will be measured in the first (midline) follow-up and, reflecting on these intermediate measures and funding availability, a decision will be made on whether the second follow-up will include biomarkers. The latter could include hemoglobin and stool sample helminth tests to check for gut infections and anemia, anthropometrics to test for stunting and wasting due to poor nutrient absorption, and cortisol tests to measure overall well-being and stress associated with improvements in living conditions. We will measure the key survey-based outcomes of interest through surveys of the children’s main caregiver, using DHS, MICS, and LSMS questionnaires as main references.

**Table 1. Key outcomes of interest**

| **Outcome Type*** | **Outcome Name** | **Definition** | **Survey** | **Analysis level** |
| --- | --- | --- | --- | --- |
| Primary | Water access | Total time spent collecting water yesterday | Household | Household |
| Primary | Water quality | Primary source of drinking water is improved source (JMP definition) | Household | Household |
| Primary | Water quantity | Total amount of water collected yesterday | Household | Household |
| **Primary** | Sanitation access | Household uses an improved latrine (JMP definition) | Household | Household |
| **Secondary** | Health behavior / Knowledge | Handwashing practices (primarily of caregiver) based on handwashing with soap + water or ash at critical junctures  Knowledge: Caregiver knows how and when to wash hands; what causes diarrhea  Sanitation practices: Cleanliness of household area and latrine (presence of flies and fecal matter); open defecation; observed indicators of toilet use –worn pathway, presence of water; improvements to latrine; disposes of child feces safely (JMP definition)  Water storage practices: has a clean pot for water that is covered | Household | Household |
| **Secondary** | Child health | Percentage of children under 5 years old with diarrhea/fever/coughing in the past two weeks; water-related mortality of children | Household | Child |
| **Secondary** | School attendance | Number of days present per child in past week, conditional on child being enrolled in school | Household | Child |
| **Secondary** | Functional water points | Number of functional improved water points in cluster; number and length of breakdowns; time to fill 5-liter jerry can; year-round availability | Village | Community |
| **Secondary** | Financial cost of water | Household water use expenses in last week | Household | Household |
| **Secondary** | Satisfaction | Satisfaction with access to water | Household | Household |
| **Secondary** | Water governance | Is there a committee that is responsible for water; size of committee and inclusion of minorities; has a water maintenance system; time since visited by health zone; satisfaction with health zone, health area and central govt. | Village | Village |

*Other outcomes not in this list may be analyzed on an exploratory basis.

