# **Hypotheses/Evaluation Questions**

The primary hypotheses this evaluation seeks to investigate pertain to the impact of the VEA program on key outcomes of interest, including: (i) access to higher quality water and improved sanitation; and (ii) reduced burden of collecting and carrying water (measured by time used for collection) especially for women and girls.

More formally, we propose to test the following primary hypotheses using the midline data:

*Hypothesis 1: VEA will improve households’ water quality*

*Hypothesis 2: VEA will improve sanitation facilities that households use*

*Hypothesis 3: VEA will increase the quantity of water that households use*

*Hypothesis 4: VEA will reduce the time spent collecting water*

In addition, there are several secondary hypotheses of interest implied by the theory of change. They address potential health and education outcomes and the mechanisms by which the inputs from VEA could produce the desired outcomes. Improvements in the water sources and in the point-of-use are related to the reduction of diarrhea, but effects can be larger if purification treatments are sustained over time (Shimamura et al. 2017). As for the participation of community members in leading the WASH projects, a study of the Community-Led Total Sanitation (CLTS) in Ethiopia and Ghana found that community engagement-led training of local leaders reduced open-defecation (Crocker et al. 2011). Another evaluation of community involvement in WASH projects in Bangladesh found that handwashing after defecation significantly improved among men, but hygiene practices before preparing, serving or eating food remained extremely low (Johnston et al. 2009). Taken together, these studies call for finding and testing the best ways to assure that the program can lead to more effective WASH governance, more sustained functionality of WASH infrastructure, reduced cost of water, and more effective community involvement including via sustained behavior change, such that the program can translate into water and sanitation gains for individuals and households. Thus, this study will also investigate the following hypotheses^[[1]](#footnote-1)^:

*Hypothesis 5*: *VEA will increase the number of functional water points in a village*

*Hypothesis 6*: *VEA will reduce the cost of water*

*Hypothesis 7*: *VEA will increase satisfaction with access to water*

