*Hypothesis 8*: *VEA will increase the probability that a village has a committee that is responsible for water*

*Hypothesis 9*: *VEA will increase the frequency with which health zone representatives visit a village*

*Hypothesis 10*: *VEA (via the behavioral change encouragement activities) will increase the frequency of improved health behaviors*

Program impacts of water and sanitation interventions have a mixed track record. Particularly for sanitation, the current experimental evidence has a wide variety of results, including many null results for diarrhea, which has often been identified as a primary outcome for these studies (Whittington et al, 2020). Reflecting on this, the research takes a cautious approach to measuring impacts. In the midline we will run exploratory analysis on health and education outcomes driven by the following hypotheses:

*Hypothesis 10: VEA will increase children’s school attendance, conditional on their enrollment*

*Hypothesis 11: VEA will reduce the incidence of diarrhea for U5 children*

The longer-term follow up survey will expand the set of outcome measures, which will be described in detail in the updated PAP.

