## Survey rounds and timeline

We plan to conduct two major rounds of household surveys: (i) a midline survey at least 12 months after the start of implementation: surveys of village leadership, WASH infrastructure, and selected households in treatment and control clusters to capture medium-term effects on main implementation outcomes such as access to improved water sources, quality of water, access to and use of improved latrines and diarrhea; and (ii) an endline survey at least 24 months after the start of implementation: surveys of village leadership, WASH infrastructure, and selected households in treatment and control clusters to capture longer-term effects.

We did not carry out a baseline prior to the rollout of project activities due to operational and timeline constraints.

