**School attendance**

- School-aged child usually attends school (Q. HH-0.19)
- Number of days school-aged child was present at school in past week, conditional on child being enrolled in school (Q. HH-0.20)

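### The attendance day count is restricted to children enrolled after randomisation, so its coefficient is an intention-to-treat effect only if VEA leaves enrolment unchanged

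*Protocol*

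**What the plan says.** The enrolment restriction appears wherever the day count is defined:

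- Hypotheses/Evaluation Questions, in the second of two hypotheses numbered 10: "school attendance, conditional on their enrollment".
- Table 1, as a secondary outcome at child level: "Number of days present per child in past week, conditional on child being enrolled in school".
- The School attendance list under the operationalised outcomes: "Number of days school-aged child was present at school in past week, conditional on child being enrolled in school".

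That last list also has a companion item with no enrolment condition: "School-aged child usually attends school (Q. HH-0.19". It is not in Table 1, the hypothesis does not name it, and no rule links it to the day count.

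On timing, Survey rounds and timeline describes "a midline survey at least 12 months after the start of implementation" and adds: "We did not carry out a baseline prior to the rollout of project activities due to operational and timeline constraints".

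The Estimation section applies equation (1) to the listed outcomes and calls the treatment coefficient the intention-to-treat effect. It reserves covariates for the under-five health outcomes, so attendance is adjusted for strata only. Hypotheses/Evaluation Questions describes the midline education analysis as exploratory.

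**The concern.** With no baseline, enrolment status is observed only after villages have been assigned and served. Selecting the analysis set on it keeps the two arms comparable only if VEA leaves unchanged who is enrolled. The protocol does not state or test that assumption.

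The assumption could fail. One of the programme's aims is "reduced burden of collecting and carrying water (measured by time used for collection) especially for women and girls". Time released from fetching water could bring a child into school as well as add days for a child already there. If newly enrolled children attend less than the others, they pull down the treated arm's mean among the enrolled even though more schooling is taking place.

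At stake is the reading of the attendance hypothesis, and possibly the design of the next round. Sample size and power calculations says midline data will supply variability and clustering estimates for some health and education measures. If attendance is among them, the definition fixed now may carry over into the endline.

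**Working it through.** The protocol states no rate, standard deviation or detectable effect for attendance, so there is no figure to reproduce. The check is algebra with assumed inputs.

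**Notation**
- e0: proportion enrolled in control (assumed 0.6 to 0.9)
- k: rise in enrolment caused by VEA (assumed 0 to 0.10)
- a: mean days per week among children enrolled under either assignment (assumed 4.5)
- b: mean days among children enrolled only because of VEA (assumed 2 to 4)
- d: true effect on days among children enrolled either way (assumed 0 or 0.1)

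**Formulas**
- Enrolled-only contrast: [e0(a + d) + k·b]/(e0 + k) − a = [e0·d − k(a − b)]/(e0 + k)
- All school-aged children, not enrolled = 0: e0·d + k·b
- The enrolled-only contrast is negative when d < k(a − b)/e0.

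**Worked case** (e0 = 0.70, k = 0.05, b = 3, d = 0)
- Enrolled only: (0.70 × 4.5 + 0.05 × 3)/0.75 = 3.30/0.75 = 4.40, against 4.50 in control: −0.10 days.
- All children: 3.30 against 0.70 × 4.5 = 3.15: +0.15 days.

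**Range with d = 0 and k from 0.02 to 0.10**
- Enrolled only, nearest zero (e0 0.9, k 0.02, b 4): −0.02 × 0.5/0.92 = −0.01.
- Enrolled only, furthest (e0 0.6, k 0.10, b 2): −0.10 × 2.5/0.70 = −0.36.
- All children: from 0.02 × 2 = +0.04 to 0.10 × 4 = +0.40.

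**With a true gain, d = 0.1**

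| e0 | k | b | Enrolled only | All children |
|---|---|---|---|---|
| 0.7 | 0 | any | +0.10 | +0.07 |
| 0.8 | 0.02 | 3 | +0.06 | +0.14 |
| 0.7 | 0.05 | 3 | −0.007 | +0.22 |
| 0.7 | 0.10 | 3 | −0.10 | +0.37 |

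Break-even d for b = 3 is 0.02 × 1.5/0.8 = 0.037 (e0 0.8, k 0.02), 0.05 × 1.5/0.8 = 0.094 (0.8, 0.05), 0.05 × 1.5/0.7 = 0.107 (0.7, 0.05) and 0.10 × 1.5/0.7 = 0.214 (0.7, 0.10). When k = 0 the enrolled-only contrast equals d exactly.

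**Precision of the all-children measure** (assumed 70% enrolled, mean 4.5 and SD 1 among the enrolled)
- Variance = 0.70(1² + 4.5²) − (0.70 × 4.5)² = 14.875 − 9.9225 = 4.95, so the SD is about 2.2 against 1.0.
- The +0.15 days of the worked case is then about 0.15/2.2 = 0.07 SD.
- If VEA adds 0.1 day for the enrolled and nothing to enrolment, the standardised effect is 0.07/2.2 = 0.03 SD over all children, against 0.1/1.0 = 0.10 SD among the enrolled.

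**The case against.** Four points can be made for the plan.

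1. **Participation is not left unmeasured.** A reader might infer that schooling is studied only among enrolled children. It is not: the usual-attendance item has no enrolment condition and could signal a shift in participation. This stands, but the item does not correct the day count and is not tied to it.

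2. **The bias is conditional.** A reader might infer that the comparison is no longer randomised. The documents do not support that as a fact. No section states or quantifies an effect of VEA on enrolment, and the route through saved time is an inference from the programme's aims. The introduction also stresses how soon the midline follows programme completion, which makes a large enrolment shift less likely. This stands. The gap is that the intention-to-treat label relies on an unstated and unchecked assumption.

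3. **Sign reversal depends on the inputs.** A reader might infer that the hypothesis would be rejected in the wrong direction. Reversal is general in the assumed range only when the true effect on children enrolled either way is zero. With a gain of 0.1 day it occurs in some scenarios and not others. If new enrollees attended as much as the rest (b = a), a true gain would be diluted but its sign would not change. A significant negative result cannot be claimed either, because no precision is given for attendance.

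4. **Days among the enrolled is a legitimate question, and zeros are costly.** Scoring non-enrolled children as zero gives a composite of enrolment and attendance with a much larger SD. This stands, and it argues for reporting both measures rather than replacing one with the other.

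The protocol's plan to control for proximity to programme schools, in Treatment and Control Groups, addresses a different threat and does not remove selection through enrolment.

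**Conclusion.** The point holds in limited form. The tabulated attendance outcome conditions on a status observed after randomisation, no baseline enrolment exists to fix the population, and the coefficient is still called intention-to-treat. Nothing else in the protocol repairs this.

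Under the assumed ranges, with VEA raising enrolment by 2 to 10 points and no effect on children enrolled either way, the enrolled-only contrast and the all-children contrast have opposite signs. A true gain among those children narrows or removes the reversal. Unchanged enrolment removes the bias altogether. The negative direction also rests on new enrollees attending fewer days than the rest. All enrolment and attendance figures here are assumptions.

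The outcome is secondary and exploratory, so no primary conclusion or power statement depends on it.

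**What to change.** 1. In Table 1, make days present in the past week over all school-aged children in sampled households, with zero for a child not enrolled, the attendance measure carrying the intention-to-treat label. Align the hypothesis with it.
2. Add enrolment by arm as an outcome in its own right, estimated with equation (1).
3. Keep the enrolled-only day count as a descriptive result or with bounds for selection (for example trimming bounds), and do not call it intention-to-treat.
4. Before coding zeros, confirm which survey item records enrolment. HH-0.19 asks about usual attendance, which may not be the same thing.
5. Settle the definition before midline variability is used to size the endline survey.

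The cost is wording, plus analysis of planned survey items if one of them records enrolment. If none does, a question is needed. The all-children measure is noticeably noisier (SD roughly 2.2 against 1.0 under the assumptions above) and mixes two margins, which is why both measures should be reported.

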# **Estimation**

We will separately estimate the main impacts of VEA on the outcomes listed above, using the following basic specification:

$y_{ihvc}= +\beta_{1}T_{c}+ \boldsymbol{\gamma X}_{ihvc}+\boldsymbol{\delta Z}_{ihvc}\boldsymbol{+}\varepsilon_{i}$ (1)

where $y_{ihvc}$ is the outcome of interest for respondent *i* in household *h* in village *v* in cluster *c* at the follow-up survey, defined above. $T_{i}$ is the treatment indicator that takes value 1 for clusters that were randomly assigned to participate in VEA (“treatment clusters”) and 0 for otherwise (“control clusters”). $\boldsymbol{X}_{ihvc}$ represents a set of strata-specific dummies where strata are based on province and number of villages in the cluster, which will equal 1 if the household falls in that stratum, and 0 otherwise. $\boldsymbol{Z}_{ihvc}$ is a vector of baseline covariates included in the analysis. Specifically we include gender and age (month) dummies for all <5 child health outcomes, but do not include covariates for other outcomes. $\boldsymbol{\gamma}$ and $\boldsymbol{\delta}$ are vectors of associated strata and covariate coefficients respectively. $\varepsilon_{i}$ is an idiosyncratic error term. Our main parameter of interest is $\beta_{1}$, the intention-to-treat effect (ITT). Standard errors will be clustered at the randomization (village cluster) level.

Our primary outcomes comprise four different measures. Our secondary outcomes comprise a broader range of variables, particularly the health behavior outcome set. To reduce the number of statistical tests and reduce the probability of false positives (Type I errors), when an outcome space is comprised of multiple variables (such as the health behavior outcomes) we combine measures into an index following (Kling, Liebman, and Katz 2007). For our four primary outcomes we use the (Benjamini, Krieger, and Yekutieli 2006) method to control the false discovery rate (FDR) and report adjusted p-values for these primary outcome measures. We do not apply this to secondary (exploratory) variables.

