We randomized these into 50 treatment clusters (containing 146 treatment villages) and 71 control clusters (containing 187 control villages). Six villages were randomly dropped to ensure UNICEF target numbers were met, while maintaining treatment and control balance.^[[3]](#footnote-3)^ We stratified randomization to ensure that the treatment and control groups are balanced with respect to their (i) province and (ii) number of villages that make up a cluster. Stratified randomization ensures that the treatment and control groups will be statistically indistinguishable from each other with respect to these characteristics, thereby avoiding bias in treatment effect.

Treatment clusters of villages will receive the status quo VEA intervention, as described above. Control clusters of villages will not receive any intervention from VEA. Data collection procedures will be identical in the two groups, as described below.

Additional discussions were held regarding the possibility of overlaying the school intervention as part of the impact evaluation. Due to the fact that the schools had been pre-selected in each province, this was not possible. There is, however, some possibility that the school intervention is differentially implemented in proximity to treatment and control villages which could threaten the validity of the results, particularly on schooling-related outcomes.

The IE team will work closely with UNICEF and local implementing partners to ensure accurate GPS and implementation tracking information is included in the planned data collection exercises to ensure that, if imbalance in proximity to treatment schools does occur, we will be able to adequately control for this in the analysis.

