# For the balance test we include:

- VEA school in village cluster
- Type of roof (improved roof= 1 if roof is finished roofing (i.e. *Metal, Wood, Calamine/Cement fiber Ceramic tiles, Cement, or Roofing shingles*)
- Wall (improved walls = 1 if walls are “finished walls”)
- Floor (improved floor= 1 if floor is “finished floor”)
- ~~Sex of respondent~~
- Household size
- Religion (Catholic = 1)
- Mother tongue
- Marital status 🡺 binary variable for married

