**Primary outcomes**

- *Water access:* Amount of time spent collecting water in minutes by the household in the previous day, calculated by summing up all trips x trip times in roster (Q. HH–A.4). Question asks: “How long did it take to fetch the water and come back on this trip, after leaving the house (including traveling there, waiting, and returning)?” for each trip.
- *Water quality*: What is the main source of drinking water for members of your household? (Q. HH–A.1). Binary outcome = 1 if response = 1 (piped into dwelling); 2 (piped into plot); 3 = piped/public tap); 5 (tube well or borehole); 7 (protected spring). Outcome is assigned 0 for all other response. (basic improved water source definition as per JMP)
- *Water quantity:* Total amount of water collected the day before interview in liters (Q. HH–A.4). Number of jerry cans multiplied by the liters in each jerry can, summed over all trips taken in previous day
- *Sanitation access:* Where do members of your household usually go to defecate (Q. HH-F.1). Binary outcome = 1 if response = 1 (flush/pour to piped sewer); 2 (flush/pour to septic tank; 3 (flush/pour to pit latrine), 6 (ventilated improved pit latrine); 7 (pit latrine with slab); 8 (composting latrine). Outcome is assigned 0 for all other responses. This follows the basic improved sanitation definition as per JMP.

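### The Estimation section's covariate rule leaves the school-attendance model without the VEA-school control that the design section provides for; adding household size to two primary outcomes is an optional precision gain

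*Protocol*

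**What the plan says.** **School proximity.** The protocol (Study Design, Treatment and Control Groups) explains that schools were chosen in advance in each province, so the school programme could not be built into the trial. It warns that uneven delivery of that programme near the two arms "could threaten the validity of the results, particularly on schooling-related outcomes". It then describes GPS and implementation tracking, collected so that "if imbalance in proximity to treatment schools does occur, we will be able to adequately control for this in the analysis".

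**Model.** The Estimation section sets one specification for all outcomes: a treatment indicator, stratum dummies and a covariate vector. The "strata are based on province and number of villages in the cluster". On covariates it says: "Specifically we include gender and age (month) dummies for all <5 child health outcomes", "but do not include covariates for other outcomes".

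**Balance test.** The list that follows the Estimation section contains "VEA school in village cluster" and "Household size". It gives no threshold, no adjusted model and no action on finding a difference.

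**Two household totals.** Under Primary outcomes, water quantity is the "Total amount of water collected the day before interview in liters". Water access is the household's collection minutes for the previous day, summed over trips. Neither is scaled per person.

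**The concern.** The plan itself names a threat to validity and says the data will allow it to be handled. The section that fixes the models then leaves no place for the handling. School attendance, where the plan expects the threat to matter most, is not an under-5 health outcome, so it gets stratum dummies and nothing else. If an imbalance appears, an analyst must either follow the Estimation section and omit the control, or follow the design section and invent one. The choice of variable, threshold and model would then be made after seeing the data, which a pre-analysis plan is meant to prevent.

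A smaller, separate matter is that litres and minutes per household are likely to rise with the number of people in the household. That variable is already on the balance list, yet it enters neither model. What is at stake there is precision and protection against chance imbalance, not validity.

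**Working it through.** **1. The statements on schools, side by side**

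| Protocol section | What it provides | School term in the attendance model? |
|---|---|---|
| Treatment and Control Groups | Control for school proximity if imbalanced; schooling outcomes singled out | Yes, if imbalanced |
| Estimation, covariates | Gender and age for under-5 health; none elsewhere | No |
| Estimation, strata | Province and number of villages per cluster | No |
| Balance-test list | School present in the cluster | Tested, with no consequence |

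No other section gives an adjusted model. The measures also differ: the design section speaks of proximity, the balance list of presence in the cluster. Even the under-5 health models contain no school term.

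**2. How large a chance imbalance could be**

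The protocol gives 50 treatment and 71 control clusters but no share of clusters with a VEA school. I assume 40%.

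- Ignoring strata: √[0.4 × 0.6 × (1/50 + 1/71)] = √(0.24 × 0.0341) = 0.090, or 9.0 points.
- Comparing within province, with the Randomization Annex counts (9/9, 20/19, 8/29, 13/14): the sum of n₁n₂/(n₁+n₂) is 4.50 + 9.74 + 6.27 + 6.74 = 27.26 (from unrounded terms), and √(0.24/27.26) = 0.094, or 9.4 points.

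Stratifying by province does not shrink this. It is the standard deviation of a chance difference in school presence. It is not a bias in attendance, and the protocol gives no effect of schools from which to derive one.

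**3. What household size could add**

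Inputs from Sample size and power calculations: 4 households in each of 332 villages is 1,328 households; 1,328/121 clusters gives m = 10.97 per cluster. The R² of household size and the ICCs of these two outcomes are not in the protocol, so both are assumed ranges. The one ICC stated, 0.7, is for use of an improved source.

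I take the variance of a cluster mean as proportional to ICC + (1 − ICC)/m, and let adjustment remove a share R² of the within-cluster part. The standard error then falls by

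1 − √{[ICC + (1 − ICC)(1 − R²)/m] / [ICC + (1 − ICC)/m]}.

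Example, ICC 0.05 and R² 0.30: before, 0.05 + 0.95/10.97 = 0.1366; after, 0.05 + 0.665/10.97 = 0.1106; 1 − √(0.1106/0.1366) = 10.0%.

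| ICC | R² 5% | R² 10% | R² 20% | R² 30% |
|---|---|---|---|---|
| 0.05 | 1.6% | 3.2% | 6.6% | 10.0% |
| 0.10 | 1.1% | 2.3% | 4.6% | 7.0% |
| 0.30 | 0.4% | 0.9% | 1.8% | 2.7% |
| 0.70 | 0.1% | 0.2% | 0.4% | 0.6% |

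If household size explained the same share between clusters as within them, the saving would be 1 − √(1 − R²), or 2.5% to 16.3% whatever the ICC. I treat the within-cluster version as the main case.

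**The case against.** The strongest reply on schools is that the two statements can coexist. The design section is conditional and speaks of being able to control, not of a firm undertaking. The Estimation section calls its equation a basic specification, which leaves room for a contingent adjusted analysis, and the balance list does plan the check. Attendance is secondary in Table 1, and education outcomes are exploratory at midline. All of this stands, and it limits the weight of the point. It does not supply the missing rule: the covariate sentence admits no exception, and nothing says what follows from a failed balance check. Nor is this detail left for another document, because the protocol presents itself as the pre-analysis plan and fixes the covariates expressly.

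A second reply concerns the remedy. A school list fixed before randomisation can differ between arms only by chance, so it cannot capture the uneven delivery that the design section fears. That is correct, and it is why realised implementation needs its own analysis.

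Three stronger readings are not supported.

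- A reader might infer that the attendance estimate is biased as planned. Chance imbalance is not bias; it is already part of the sampling uncertainty. Whether delivery will in fact differ by arm is unknown.
- A reader might extend the school threat to hygiene behaviour. The protocol singles out schooling outcomes and does not name hygiene.
- A reader might call the omission of household size an error in two primary outcomes. It is not one. The hypothesis on water quantity concerns what households use, so a household total is a legitimate target, and the unadjusted intention-to-treat effect on it is unbiased. The covariate vector is defined as baseline, and Survey rounds and timeline states that no baseline was carried out, so leaving out a midline variable is defensible.

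**Conclusion.** The point holds for schools as a conflict of wording with a practical consequence: the design section provides for a control if there is imbalance, the Estimation section excludes it, and the balance list does not bridge the two. The conflict takes effect only if an imbalance appears, and it bears mainly on an outcome that is exploratory at midline. An imbalance of the order of 9 points would be unremarkable if about 40% of clusters had a VEA school. That share is assumed, and no effect on the attendance estimate can be calculated from the protocol.

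Household size is an optional improvement. The likely saving is about 1 to 10% of the standard error at ICC 0.05 to 0.10 and under 1% at ICC 0.7, with R² assumed at 5 to 30% and acting within clusters. If collection time clusters as strongly as the protocol assumes for source use, the gain for that outcome is negligible.

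**What to change.** **Schools.** In the Estimation section:

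1. Include in every school-attendance model an indicator for whether the cluster contains a school on the pre-selected list. First confirm that the list was fixed before the villages were randomised. Include it whatever the balance test shows, and drop the condition on observed imbalance from the design section.
2. Name a sensitivity analysis that uses realised school implementation or proximity from the GPS tracking, and define the measure. It should not be the main adjustment, because realised works may respond to village assignment. It is still needed, because the list does not capture differential implementation.
3. Align the design section and the balance list with this rule.

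**Household size (optional).** Pre-specify it as a covariate for water quantity and collection time, and report the unadjusted estimate alongside. The drawback is that it is measured at midline, so adjustment assumes that the programme does not change household size.

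**Cost.** A few sentences of wording. No additional survey data are needed: the tracking is already planned, and both the school variable and household size are on the balance list.
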